## Abstract

•IVR games can enhance cognitive and motor training in mild neurocognitive disorders.•IVR games support cognitive and motor function non-pharmacologically.•Combining fun and rehab to boost motivation and tech inclusion in older adults.•IVR games offer an affordable and accessible option for middle-income countries.•IVR Games may help delay Alzheimer’s in mild neurocognitive disorder.

IVR games can enhance cognitive and motor training in mild neurocognitive disorders.

IVR games support cognitive and motor function non-pharmacologically.

Combining fun and rehab to boost motivation and tech inclusion in older adults.

IVR games offer an affordable and accessible option for middle-income countries.

IVR Games may help delay Alzheimer’s in mild neurocognitive disorder.

## Introduction

The older population, which has grown drastically since the beginning of the 21st century, is at a considerably higher risk of brain-aging-related issues.^1^ As the proportion of older individuals increases within the general population, the number of neurocognitive disorders in gerontological practice also rises. Among other challenges, this demands effective interventions for prevention and gerontological rehabilitation.^1^^,^^2^

Mild Neurocognitive Disorder (NCD), also known as mild cognitive impairment, is defined as cognitive decline beyond what would be expected for age and education in one or more cognitive domains (complex attention, executive functions, learning and memory, language, perceptual-motor, or social cognition) based on concerns of the individual, caregiver, or clinician. Yet, these changes do not interfere with the ability to remain independent in daily activities.^3^ It is common in older populations, and its prevalence increases with age.^4^ It is estimated that the global prevalence of mild NCD is between 15 % and 20 % among people aged 60 and older.^5^

Approximately 80 % of patients with mild NCD will have converted to Alzheimer's Disease (AD) after approximately six years of follow-up.^6^ Therefore, the predicted risk of this conversion and the early identification of high-risk mild NCD participants are urgently needed. Since AD is irreversible and faces significant treatment challenges, the key to preventing and treating AD is to take early preventive and intervention strategies. The mild NCD stage provides a “window of opportunity” for AD prevention and treatment.^7^^,^^8^

Based on neuroplasticity, cognitive interventions can provoke brain changes and generate new functional connections.^9^ Thus, to slow the progress of neurodegenerative dementia, cognitive training has been suggested as an approach to improve impaired brain functions.^10^^,^^11^

Another non-pharmacological intervention, in addition to cognitive training, that can help improve mood and preserve cognitive functions is physical exercise,^12^ which can enhance brain metabolism and brain-derived neurotrophic factor, supporting brain plasticity and hippocampal angiogenesis.^13^ Multidomain or multimodal interventions, consisting of two or more interventions, may have even more significant benefits than cognitive training or exercise alone.^14^

A new and promising tool to improve cognitive functioning is Virtual Reality (VR) .^2^^,^^15^ VR is defined by Lange and Pompeu as follows: a three-dimensional environment presented on a screen with which the user can interact using movements or gestures tracked by sensors, gloves, tracking devices, or touchscreens.^16^ VR technology uses human senses (vision, touch, movement) in a virtually created environment. Its advantage is the ability to simulate real-life experiences in a pre-created virtual environment and provide short-term feedback^17^ according to the individual's performance.^18^

VR allows users to experience and interact with computer-generated environments and, in some games, react as they would in real life when performing predetermined tasks.^19^ This method can be used to engage in fun and exciting tasks, thus increasing user motivation.^20^ VR health applications have been evaluated in various studies to address health-related issues in older adults.^21^

Immersive technologies allow users to isolate themselves from the physical world, explore the virtual environment, and create mental representations of the virtual environment, leading to the experience of spatial presence.^22^ Neurological evidence further indicates that the experiences of spatial presence induced by immersive media would increase activity in brain regions associated with cognitive functions.^1^^,^^23^

VR systems within the rehabilitation context can be grouped into systems customized for rehabilitation and commercial systems aimed at a broader entertainment market. The advantage of customized systems developed for rehabilitation is that they follow rehabilitation principles and, therefore, can be intrinsically valuable. On the other hand, commercial systems may be more cost-effective, entertaining, and of higher product quality, but in turn, they require adaptation to find their place as a rehabilitation tool.^24^

The Head Mounted Display (HMD) represents the most immersive VR technology. The literature on HMD-based VR for cognitive rehabilitation is limited. Rehabilitation approaches tested with HMD VR include customized software.^25^ Combining commercial hardware and software enables a more economically sustainable approach by avoiding the development of customized systems, which often entail high costs. This approach not only reduces operational costs in healthcare institutions but also has the potential to slow the progression of cognitive and motor deficits, generating economic benefits by reducing the need for advanced care in the future. This strategic integration can serve as a foundation for public health policies aimed at active aging and the technological inclusion of older populations.

## Objective

To analyze the acceptability and effects of immersive VR combining commercial hardware and software in individuals with mild NCD or mild major NCD and compare it with a motor-cognitive integrated intervention.

### Hypotheses

1.VR interventions will significantly improve postural control, gait, functionality, cognition, and mood more than the motor-cognitive integrated intervention.2.The authors hypothesize that participants undergoing VR interventions will improve their performance in the games.3.The authors expect that commercial VR games will be acceptable to older adults with mild NCD or mild major NCD. Although this population may not be familiar with this technology, commercial games were developed for entertainment in an attractive and motivating virtual environment and were easy to use.

### Study design

The study will be a randomized, controlled, and blinded clinical trial. Participants will be divided into two groups: the VR group (VRG) and the exercise group (EG). The study assessments will be conducted before and after the intervention.

## Methods

### Study location

All participants will be recruited from the Older People Memory Clinic of the Clinical Hospital, School of Medicine, University of São Paulo, Brazil.

### Eligibility criteria

#### Inclusion criteria

The following will be included: 1) Older people individuals (> 60-years-old); 2) Both genders; 3) Adequate proficiency in the Portuguese language; and classified in one of the following two categories: (3) Mild NCD – at least one domain with a composite score less than or equal to −1, but without criteria for dementia; (4) Mild Major NCD with a CDR (Clinical Dementia Rating scale) <2; and (5) Agreeing to participate in the study by signing the consent form.

#### Non-inclusion criteria

The following older people individuals will not be included; 1) Presence of delirium, psychotic mental disorders, or substance-related mental disorders, according to DSM-5 criteria; 2) Severe retinal problems or severe visual deficits even with corrective lenses; 3) Uncorrected severe hearing loss; 4) Those with decompensated cardiovascular diseases, such as angina or heart failure; 5) Epilepsy; 6) Motion sickness; 7) Any health issue that prevents them from using VR; 8) Severe clinical conditions with uncontrolled symptoms or instability.

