#### Exclusion criteria

Participants who experience cybersickness during the familiarization session and those who miss the first two consecutive sessions will be excluded. Additionally, participants must complete 100 % of the training sessions to remain in the study. They may miss up to 20 % of the sessions, provided that all missed sessions are made up through compensatory sessions, to be scheduled in agreement with the research team.

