### Selection and description of motor-cognitive integrated intervention

Table 2 describes the exercises of the motor-cognitive integrated intervention.

**Table 2 tbl0002:** Brief description of the exercises.

Description of Multimodal Exercises with integrated cognitive interventions	
Individually supervised interventions by a trained physical therapist. Twice a week, for 45-minutes, over 7-weeks. First day: Exercises 1, 2, 4, 6, 8, and 10. Second day: Exercises 1, 3, 5, 7, 9, and 10.	
**Description**	**Materials**
1. Walking while the participant verbalizes words with the same pre-determined phonetic initial.	None
2. During the plantar flexion movement, the individual must touch colored markers positioned on the wall in a random order pre-defined by the researcher.	Colored EVA circles
3. Execution of a circuit consisting of activities using proprioceptive discs and unstable surfaces, combined with simple mathematical calculations.	Proprioceptive disc and 6 mats (55 × 95 × 3 cm)
4. Performing ball-throwing exercises while the participant verbalizes words belonging to specific semantic categories.	Inflatable ball (20 cm)
5. Performing exercises on a step platform with load, alternating legs according to pre-defined instructions.	Step platform (60 × 28 × 10 cm)
6.Memorizing the stacking order of cones on a chair and replicating this order on another chair positioned 3 m away.	6 colored cones and 2 chairs
7. Maintaining static balance on an unstable surface while the participant claps upon hearing a specific letter of the alphabet announced by the researcher.	3 mats (55 × 95 × 3 cm)
8. Hip adduction exercise with a ball between the knees and hip abduction against elastic resistance around the knees, while the participant recalls and describes figures from a previously presented image.	Inflatable ball (20 cm), elastic band, and printed images
9. Walking with arms extended while holding a ball, performing upper limb abduction movements according to opposite verbal commands.	Inflatable ball (20 cm)
10. Stretching.	None

Physiotherapists and neuropsychologists mutually agreed to select the exercises and games according to the specific demands. The cognitive and motor demands of the games and exercises were then paralleled, illustrated in Fig. 1, Fig. 2.

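### Entry screening tests fitness for VR but not for the exercise programme; with the full-completion rule, this risks unequal exclusions after randomisation

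*Protocol article*

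**What the plan says.** Under Non-inclusion criteria, item 7 is an arm-specific catch-all: "Any health issue that prevents them from using VR". Item 6, "Motion sickness", also reads as directed at VR. Two items are general and apply to everyone: item 4, "Those with decompensated cardiovascular diseases, such as angina or heart failure", and item 8, "Severe clinical conditions with uncontrolled symptoms or instability". Neither the inclusion nor the non-inclusion list mentions the exercise programme, mobility or balance.

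Table 2 describes that programme. Exercise 5 is "Performing exercises on a step platform with load, alternating legs according to pre-defined instructions". Exercise 3 is "Execution of a circuit consisting of activities using proprioceptive discs and unstable surfaces, combined with simple mathematical calculations". Others involve static balance on an unstable surface, resisted hip work, and walking while holding a ball.

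The Exclusion criteria add a VR-tolerance rule and an attendance rule: "Participants who experience cybersickness during the familiarization session and those who miss the first two consecutive sessions will be excluded". They also state that "participants must complete 100 % of the training sessions to remain in the study"; up to 20 % of sessions may be missed, but only if all are made up. Table 4 puts the initial physical assessment and allocation on Day 2. It does not show the familiarization session.

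**The concern.** A randomised comparison of two training programmes works best when everyone randomised could take up either one. Here, unsuitability for VR is meant to be found before allocation, while unsuitability for the exercises can surface only afterwards. Make-up sessions do not help someone who cannot do the tasks, so the completion rule turns that inability into removal from the study.

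Those removed would plausibly be among the weaker participants on balance and gait. The Mini-BESTest and Dynamic Gait Index are clinical outcomes, and hypothesis 1 claims superiority of VR on postural control and gait. If the arms lose different kinds of people, the completers are no longer the groups that randomisation formed.

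**Working it through.** **1. Is the screen asymmetric?**

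| Reason a person could not do the assigned training | VR | Exercise |
|---|---|---|
| Arm-specific health item at entry | item 7, and probably item 6 | none |
| Decompensated cardiovascular disease; severe unstable conditions | items 4 and 8 | items 4 and 8 |
| Unable to stand | item 7, because the games are played standing | caught indirectly by item 7 |
| Stable limitation affecting loaded stepping, unstable surfaces or walking tasks | item 7, if it also prevents VR use | only if it also prevents VR use |
| Cannot complete after allocation | removed | removed |

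The fourth row is the gap.

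**2. The plan's own figures.** The article gives no rate of inability to exercise and no dropout by arm. It gives 32 participants, 16 per arm, with 20 % dropout overall, 80 % power, two-sided α 0.05 and an effect size of 0.29 whose metric is not named. The total can be reproduced as a group-by-time interaction if 0.29 is Cohen's f and the pre-post correlation is 0.5 (both my assumptions): λ = f²·N·m/(1−ρ) = 0.0841 × 26 × 2/0.5 = 8.75, power 0.81 at N = 26. Then 26 × 1.2 gives 32, and 26/0.8 gives 33. This only sets a baseline for step 5.

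**3. Chance that the problem occurs.** If a proportion p of those allocated to exercise could not do the programme, the chance of at least one among 16 is 1 − (1 − p)^16. For assumed p of 5 %, 10 % and 20 % this is 0.56, 0.81 and 0.97. Each such person is 1/16 = 6.25 percentage points of that arm.

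**4. Shift in the retained arm's mean.** For 16 standard normal values, the three lowest have expected values of about −1.77, −1.28 and −0.99. If the k lowest are removed, the mean of the rest rises by:
- k = 1: 1.77/15 = 0.12 SD
- k = 2: 3.05/14 = 0.22 SD
- k = 3: 4.04/13 = 0.31 SD

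These figures assume that those removed are exactly the lowest on the outcome. If inability correlates 0.5 with the outcome, they halve to 0.06, 0.11 and 0.16 SD.

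They are shifts at a single time point. Data analysis plans a repeated-measures GLM on pre and post values, and a removed participant leaves both. With equal SDs at the two times, the shift in mean change is (r_post − r_pre) × the figure above. Equal correlations give zero. With two lost and correlations differing by 0.2, the shift is 0.2 × 0.22 = 0.04 SD, in either direction.

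**5. Precision.** Under the reading in step 2, noncentrality = 4f/√(2(1−ρ)(1/n₁ + 1/n₂)). With 20 % loss in both arms (13 v 13), power is 0.81. Extra loss in the exercise arm alone of 10, 20 or 30 points (13 v 11, 13 v 10, 13 v 8) gives 0.77, 0.75 and 0.69. The extra losses are assumed.

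**The case against.** The strongest reply is that the gap may be small. The games are played standing and were selected for their motor demands. The article says the cognitive and motor demands of games and exercises were paralleled, and the exercise sessions are individually supervised. Items 4 and 8 apply to everyone. Someone unable to stand and move through a 45-minute VR session is already barred. The figures showing the paralleling are not available, so the difference in physical demand cannot be checked. This limits how many people could be affected. It does not close the gap: the figure captions describe the domains and skills stimulated, and do not say that capacity for one programme implies capacity for the other.

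A reader might infer that inability to train arises only in the exercise arm and that the result is biased towards VR. The documents support neither. The completion rule applies to both arms, and VR participants may still fail in later sessions. Table 4 does not say whether familiarization precedes allocation. If it follows allocation and only the VR arm attends, cybersickness exclusions fall on the VR arm alone. If everyone attends before allocation, the asymmetry against the exercise arm is stronger.

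As for direction, losing its weakest members raises the exercise arm's final motor mean, which works against VR. Only the comparison of adherence would clearly favour VR.

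**Conclusion.** The asymmetry stands on the text: fitness for VR is an entry condition, fitness for the exercise programme is not, and the general criteria fill the gap only in part. With removal of non-completers, this creates a risk of differential exclusion after randomisation, plausibly more in the exercise arm.

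Its size and net direction cannot be determined from the documents. The 0.06 to 0.31 SD range illustrates one to three losses, applies to a mean at one time point, and would partly cancel in the pre-post analysis. What matters there is how inability relates to change, on which the documents give nothing. The point merits correction because arms of 16 are sensitive to single losses and the remedy is cheap. It does not show that the trial's result will be biased in a known direction.

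**What to change.** 1. Extend item 7 so that, after "Any health issue that prevents them from using VR", it continues: or from performing the motor-cognitive exercise programme (Table 2).
2. Judge the item for every candidate before allocation, using the physical assessment already scheduled on Day 2.
3. Place the familiarization session and its cybersickness exclusion before allocation for all candidates, and show it in Table 4.
4. Keep all randomised participants in follow-up and in the analysis, and report completion of sessions by arm with reasons. Without this step the completion rule would still turn any remaining inability into selective loss.
5. For those already enrolled, record from baseline data whether they would have met the reworded criterion.

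Cost: a formal amendment by the route in Protocol amendments, a familiarization session for people who may go to the exercise arm, and a few otherwise eligible people not enrolled. Trial status reports about 50 % recruited, so roughly half the sample will have entered under the existing rule; step 5 lets that be described.

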#### Exclusion criteria

Participants who experience cybersickness during the familiarization session and those who miss the first two consecutive sessions will be excluded. Additionally, participants must complete 100 % of the training sessions to remain in the study. They may miss up to 20 % of the sessions, provided that all missed sessions are made up through compensatory sessions, to be scheduled in agreement with the research team.

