### Interventions

Participants will be randomly assigned to the VRG or EG groups, with an allocation ratio of 1:1. Participants in the VRG will participate in 14 IVR training sessions lasting 45 min, twice a week. The Oculus Quest 2 Advanced 128Gb VR Headset will be used, attached, and adjusted to the participant's head. A BOBOVR M2 Pro adapter will be used for greater comfort, a support that offers greater comfort, and a magnetic battery with quick replacement and charging and two wireless handheld controllers. In each training session, participants will play three games on odd days and another three games on even days. A trained physiotherapist will accompany all sessions to correct the participants' movements and posture through manual guidance and verbal cues. The level of difficulty progression will be according to the participant's performance. Scores will be recorded for learning analyses. The time required to change the game will be approximately three minutes, and participants will sit in a chair during this period. Individuals in the EG will participate in 14 training sessions of a motor-cognitive integrated intervention, lasting 45 min and having a frequency of twice a week. A trained physiotherapist will conduct the sessions.

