### Participant timeline

Table 4 illustrates the study participant enrollment process, intervention, and timing of assessments.

**Table 4 tbl0004:** Activity timeline.

	Day 1	Day 2	Days 3‒16	Day 17
Eligibility screening	x			
Initial neuropsychological assessments	x			
Informed consent	x			
Initial physical assessments		x		
Allocation Interventions		x		
			x	
Final neuropsychological assessments				x
Final physical assessments				x

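### Attendance exclusions act after randomisation and before the only post-treatment assessment, so effects and VR acceptability are estimated in completers, and removal may differ by arm

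*Protocol article*

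**What the plan says.** Under Eligibility criteria, separately from the non-inclusion list, the protocol article has a subsection headed Exclusion criteria. It states: "Participants who experience cybersickness during the familiarization session and those who miss the first two consecutive sessions will be excluded". It continues: "participants must complete 100 % of the training sessions to remain in the study", with an allowance: "They may miss up to 20 % of the sessions, provided that all missed sessions are made up through compensatory sessions".

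Table 4 (Participant timeline) has the entry "Allocation Interventions", which the text extraction has run together. Read with its marks, it puts allocation on Day 2, interventions on Days 3–16 and the final neuropsychological and physical assessments on Day 17. Both arms have 14 training sessions (Interventions). The familiarization session is mentioned only in the exclusion criteria and has no row in Table 4.

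The Objective begins: "To analyze the acceptability and effects of immersive VR combining commercial hardware and software". Acceptability is measured by a satisfaction questionnaire and feasibility by game scores (Outcome measures of acceptability). The Assessments section says that the blinded researcher evaluates every participant before and after the intervention. The Data analysis section names no analysis set.

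**The concern.** Missing the first sessions and not completing the course both happen after allocation, and the assigned intervention can cause either. If such participants leave the study, they have no Day 17 value and drop out of the comparison that randomisation was meant to protect. What remains is a comparison of people who finished one programme with people who finished the other.

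Acceptability has a second problem. People made ill by the headset, or who stop coming, are the clearest evidence that VR is not acceptable to them. Removing them leaves the questionnaire to those who tolerated and finished VR. For cybersickness this holds whether familiarization comes before or after allocation. The article describes the trial as preliminary work for a definitive one (Dissemination policies), so tolerability and retention are among the things it most needs to report.

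**Working it through.** **1. Order of events.** Allocation is on Day 2, training on Days 3–16 and the outcome on Day 17. Days 3–16 are 16 − 3 + 1 = 14 slots, which the 14 sessions fill. Both attendance rules therefore act between allocation and outcome. No slot is left for familiarization after Day 2, and none is shown for it before. Whether it precedes allocation, and whether the exercise group attends, cannot be read from the article.

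**2. The two attendance rules against each other.** The allowance is 0.20 × 14 = 2.8, so 2 whole sessions. Missing the first two is 2/14 = 14.3%, inside the allowance, yet the preceding sentence excludes that participant.

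**3. Possible bias in the comparison (all inputs assumed).** Suppose there is no true effect, tolerance is standard normal, and it correlates ρ with the outcome. Removing the least tolerant fraction p of one arm shifts that arm's mean by ρ × φ(z_p)/(1 − p) SD, where φ is the normal density and z_p the p-quantile.

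| p removed, VR only | φ(z_p)/(1 − p) | ρ = 0.3 | ρ = 0.5 |
|---|---|---|---|
| 0.10 | 0.1755/0.90 = 0.195 | 0.06 | 0.10 |
| 0.20 | 0.2800/0.80 = 0.350 | 0.10 | 0.17 |
| 0.25 | 0.3178/0.75 = 0.424 | 0.13 | 0.21 |

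If 10% of the exercise group are removed in the same way, subtract 0.195 before multiplying by ρ:
- 20% removed from VR: 0.155ρ = 0.05 to 0.08 SD.
- 25% removed from VR: 0.229ρ = 0.07 to 0.11 SD.

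A simulation with 16 per arm and the 3 least tolerant removed from VR only gave a bias of 0.09 SD (ρ = 0.3) and 0.16 SD (ρ = 0.5). The two-sided type I error was 5.9% and 7.4% against a nominal 5%.

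**4. Acceptability (inputs assumed; 20% equals the dropout rate in the Sample size section).** With 20% removed and 90% of the rest approving, 90% is reported. Of all allocated to VR, 0.80 × 0.90 = 72% approve if none of those removed do, and 72% + 20% = 92% if all of them do. In head counts out of 16, with none of those removed approving:
- 1 removed: 0.9 × 15/16 = 84%.
- 3 removed: 0.9 × 13/16 = 73%.
- 5 removed: 0.9 × 11/16 = 62%.

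**5. Can the bias be expressed as a share of the planned effect?** The plan gives an effect size of 0.29 and N = 32 but not the metric.
- As a standardised mean difference: 2 × (1.96 + 0.84)²/0.29² gives 187 per arm, 374 in total before dropout. This does not reproduce 32.
- As Cohen's f for a 2 × 2 group-by-time interaction with an assumed pre-post correlation of 0.5: N = 26 (power 0.81), and 26 × 1.2 = 31.2, so 32. This reproduces the figure.

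On the second reading the noncentrality is 0.29² × 26 × 2/0.5 = 8.75. With 13 per arm this corresponds to √8.75/√(13/2) = 1.16 SD of change. A bias of 0.06–0.21 SD is then 5–18% of the planned effect on this reading, against 21–72% on the first. No single percentage can be quoted.

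**The case against.** **An analysis plan that is not shown may define an intention-to-treat set.** It may. It cannot recover Day 17 outcomes that were never measured, and it would conflict with the requirement to complete all sessions in order to stay in the study.

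**The exclusions may mean only that training stops.** The Assessments section, which has every participant evaluated twice, is compatible with that reading. The exclusion wording is not, so the two sections need reconciling.

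**A reader might infer that removal differs by arm.** The article does not support this as a fact. The attendance rules are worded identically for both groups. The cybersickness rule would be one-sided only if familiarization follows allocation or is given to the VR group alone, and the article says neither. Its place under Eligibility criteria fits a check of everyone before allocation equally well, and then that part of the between-arm bias is zero. Motion sickness and health problems that prevent VR use are already non-inclusion criteria for both arms, which should lower the rate. What stands is the risk: reasons for abandoning a headset programme and an exercise programme can differ under identical rules.

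**The bias is small next to the noise.** With 13 completers per arm the standard error of the difference is √(2/13) = 0.39 SD, and the type I error rises only moderately. This is correct on the inputs used. The removal rates and correlations are assumptions, and VR-only removal is the unfavourable case.

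**Not everyone removed disapproves of VR.** Some will leave for unrelated reasons, so 72% is a floor.

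**Conclusion.** The point holds in a limited form. As written, randomised participants are removed for early absence or non-completion (after any make-up sessions) before the only post-treatment assessment, so the efficacy comparison is among completers. VR acceptability and feasibility are measured in those who tolerate and finish VR, and acceptability is probably overstated.

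Unequal removal between arms is possible but not established. Its size depends on assumptions: about 0.06–0.21 SD if 10–25% leave the VR arm only, and about 0.05–0.11 SD if 20–25% leave VR and 10% leave the exercise group, both with a correlation of 0.3–0.5 and no true effect. In these illustrations the bias favours VR because of how they are set up; the direction in the trial itself is uncertain. A reader might also want to express the bias as a share of the planned 0.29, but its metric is not stated, so the article supports no such percentage. For acceptability, a reported 90% could correspond to as little as 72% of those allocated.

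The correction should be made now: about half the sample is recruited (Trial status), and unmeasured Day 17 outcomes cannot be recovered later.

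**What to change.** 1. Separate stopping training from leaving the study. Invite every randomised participant to the Day 17 assessment whatever their attendance, make the main comparison by allocated arm, and label the analysis of 100% completers as secondary. This does not alter when anyone stops training.
2. State in Table 4 when familiarization takes place and who attends. Anyone removed after allocation stays in the analysis by allocated arm. Checking everyone with the headset before allocation would make the rule symmetric, but it exposes future exercise-group participants to VR. That is a trade-off for the investigators and not a required part of this fix.
3. Report cybersickness exclusions and non-completions by arm, with reasons, next to the questionnaire and game scores, with everyone familiarized or allocated as the denominator. The questionnaire itself need not change.
4. Reconcile the exclusion for missing the first two sessions with the 20% make-up allowance, and the exclusion criteria with the Assessments section's statement that everyone is assessed twice.

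The cost is a small amendment with about half the sample already recruited, a Day 17 visit for a few non-completers, and possibly a diluted effect estimate, because people who trained little will count in their allocated arm.
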